### Phase II: recruitment, screening, randomization, and survey administration

#### Recruitment and screening

The sample will include blacks recruited from barbershops, salons, and faith-based organizations in New York City. We intend to screen approximately 1250 blacks and expect that approximately 398 will be enrolled in the study (Figs. 2 and 3). Research assistants will screen potential participants to determine eligibility on a wide range of exclusion and inclusion criteria at community-based settings such as faith-based organizations, barbershops, beauty salons, health fairs, and community-based organizations. If participants are eligible, research assistants will provide informed consent (Additional file 1). Participants will be re-consented if procedures of study significantly change.

**Fig. 3 Fig3:**
[figure not shown]
Study design

**Fig. 4 Fig4:**
[figure not shown]
SPIRIT checklist

##### Eligibility criteria (inclusion and exclusion)

Eligible participants will (1) self-report their race/ethnicity as black, African American, or African ancestry; (2) be ≥ 18 years old; (3) accessible by telephone or cellphone; (4) have no plans to move away from the region within the year following enrollment; (5) consent to participate in the study, which includes permission to release medical record information; and (6) have a positive screening for OSA, based on whether an individual receives a score ≥ 6 on the ARES Questionnaire. Participants are ineligible if they (1) are involved in another sleep study; (2) know someone who is participating in this study; (3) plan to move away in the next year; (4) had a heart attack or stroke within the past 12 weeks; (5) are pregnant; (6) refuse to use the ActiGraph activity monitor; (7) are non-English speaking; or (8) refuse to use the WatchPAT™ home sleep test device. Participants who are currently being treated for sleep apnea will not be eligible for the study. We do not anticipate that concomitant treatment for other medical conditions will preclude participation in the study.

#### Survey data collection

##### Measures at baseline, 6-month and 12-month follow-up

Participants will complete the ARES™ [74], Center for Epidemiologic Studies Depression Scale [75, 76], Apnea Knowledge Test [77], Functional Outcomes Sleep Questionnaire [78], Medical Outcomes Study Short Form [79, 80], Self-Efficacy Scale [81], and Change Assessment Scale [82] (Fig. 3, Additional file 2).

##### Sociodemographic variables

Sociodemographic variables will include age, type of health insurance, marital status, education, place of birth (for example, US vs. Caribbean), years in current residence and locality, number of children living in household, number of adults living in household, self-described ethnicity, and annual household income.

##### Epworth sleepiness scale

This questionnaire uses a Likert-type scale in which the respondent indicates the most appropriate number ranging from 0, would never doze or sleep, to 3, high chance of dozing or sleeping, based on a given situation. A score of 10 or more is considered excessive sleepiness [83].

##### Apnea Knowledge Test (AKT) and Apnea Beliefs Scale (ABS)

These two questionnaires assess participants’ understanding and beliefs of OSA and CPAP treatment. The AKT includes 13 questions with a yes/no response choice and 2 open-ended questions; the ABS includes 24 items on a 5-point Likert scale ranging from ‘strongly agree’ to ‘strongly disagree’. A higher score on the AKT indicates better knowledge and understanding of the illness and treatment and a higher score on the ABS indicates greater likelihood of adherence to treatment [84].

##### Change assessment scale

This is a 32-item instrument that assesses a person’s readiness to change. Participants evaluate the extent to which they strongly agree or strongly disagree with various statements such as “I’ve been thinking that I might want to change something about myself” and “I have problems and I really think I should work on them” [85].

##### Medical history

Medical history includes family history of sleep disorders, obesity, diabetes mellitus, hypertension, dyslipidemia, and CVD, history of other preventive behaviors (for example, prostate exams), and other health behaviors (for example, regularity of physical examinations, cholesterol screening, smoking and drinking habits, and exercise habits).

##### Apnea-Risk Evaluation System (ARES) questionnaire

We will use the ARES to identify individuals who are at high OSA risk. This tool includes questions on sleep patterns, daytime functioning, knowledge of sleep apnea, and diseases associated with sleep apnea (that is, hypertension, diabetes mellitus, heart disease) [86]. Other data solicited in the ARES include sociodemographic information, medical comorbidities, the Epworth Sleepiness Scale, and frequency of breathing abnormalities. The questionnaire has a sensitivity of 0.94, specificity of 0.79 (based on a clinical cut-off of apnea-hypopnea index (AHI) > 5), positive predictive value of 0.91, and negative predictive value of 0.86 [87]. Our rationale for using the ARES questionnaire in a diverse sample is also based on findings in our previous studies [73, 88, 89], which indicated that the ARES accurately detected OSA risk among black participants. Other evaluation tools, such as the Berlin, the American Society of Anesthesiologists checklist, or STOP-BANG, have not been specifically tested among blacks at the community level.

#### Data collection and management

Once baseline data is obtained, contact information of consenting participants will be provided to the data manager, who will maintain a registry of enrolled participants (control group and intervention group). This registry will be used to track them during the study period. Using computer generated schedules; the data manager will perform blind outcome ascertainment at 6 and at 12 months.

The data manager will perform interim analysis to ensure that selection and attrition biases do not occur if refusal occurs after recruitment or randomization. Selection bias might result from participant’s refusal to participate and attrition bias could result in an unbalanced design. Appropriate statistical techniques, such as Heckman 2-stage approach (Generalized Estimation Equations (GEE) Probit Model) [90] and Monte Carlo (EM algorithm) [91] analysis, will be used to address such biases or problems that might result from missing data. Adequate statistical corrections will be made in final statistical analyses to increase the generalizability of findings. Sociodemographic data obtained from those who did not participate will be used to determine whether individuals who did not participate are similar to those in the study (selection bias). Likewise, baseline characteristics of those who withdrew from the study will be contrasted with completers to determine whether any attrition bias may have occurred. Site-specific effects (shops vs. salons vs. faith-based site) will also be examined. If these analyses reveal meaningful between-group differences, such characteristics will be treated as covariates. If we identify missing data in the analysis (e.g., logs, checklists, rapport), we will use Kelsey’s method strategies to remedy missing data [92]. Although we do not plan to perform extensive cost-benefit analysis, we will document implementation costs (e.g., personnel, training costs, home visits, and postage and handling). In addition to performing analytical tests to minimize the potential confounding effects of missing data, we will engage in evidenced-based research design (recruitment and retention) strategies to minimize the possibility of missing data, some of which include (1) closely monitoring research milestones and targets and ensuring that participants reach these with the help of a health educator with whom the participants have a good rapport; (2) limiting the amount of research burden; (3) keeping close contact with participants through the project coordinator or health educator; and (4) providing adequate and fair monetary incentives for participating in the research study.

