## Methods and design

In a two-arm, randomized controlled trial, we will ascertain effectiveness of peer-based sleep health education and social support in increasing OSA evaluation and treatment rates among 398 blacks at risk for OSA (198 participants in treatment group and 198 participants in attention-control group), over a 12 month period. Participants in the intervention arm will receive quality-controlled, culturally, and linguistically tailored peer education using a sleep health education manual developed based on principles of motivational enhancement. Participants in the treatment arm will each receive up to five peer-based sessions promoting OSA evaluation. Those with an OSA diagnosis will receive five additional peer-based sessions promoting OSA treatment compliance and adherence from a peer health educator contingent upon poor treatment adherence from CPAP-based reports. Those in the attention-control arm will receive standard OSA literature from the study staff. Regardless of group assignment, we will ascertain all outcomes at baseline and at 6- and 12-month follow-up assessments.

The study was approved by the New York University Langone Health Institutional Review Board and all participants will be consented by study staff before enrollment. The trial is in accordance to the Consolidated Standards of Reporting Trials (CONSORT) Statement on randomized trials for non-pharmacological treatment and the Standard Protocol Items: Recommendations for Interventional Trials SPIRIT checklist (see Additional file 1 for CONSORT Figure, SPIRIT Figure and checklist Figs. 2 and 3) [37, 38].

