#### Randomization to intervention or attention-control groups: allocation and blinding

Participants will be randomly assigned to either the intervention arm (partnered with a peer health educator who received the culturally and linguistically tailored sleep health education and was trained for 8 weeks) or the attention-control group (the comparative group where participants are partnered with a peer health educator who did not receive tailored sleep health education but only standard health training for a 1 hour session). The unit of randomization is the participant and thus the unit of analysis will be at the participant level. All study staff except for the data manager and project coordinator will be blinded to participant assignment. The data manager generates the randomization sequence for each eligible participant and the study coordinator randomly assigns peer health educators to participants assigned to treatment and attention-control groups. We will un-blind participant assignment only in cases where the participant’s health is at risk due to CPAP usage (Fig. 3).

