
After the home sleep study, the study staff will provide the results to the study physician to determine the risk of sleep apnea from the WatchPAT™ home sleep recorder device. The study physician will discuss the home study results with all participants and will recommend treatment to those meeting OSA diagnostic criteria (AHI > 10). Participants who do not meet OSA diagnostic criteria will be transferred to the project coordinator either for study close-out since they no longer need to continue their participation in the study, for future clinic-based diagnostic assessment, or for treatment customization. Participants who are at risk for OSA will be referred for further diagnostic assessment and treatment to a sleep clinic accredited by the American Academy of Sleep Medicine. Expenses incurred from laboratory and CPAP procedures recommended by sleep clinicians in our catchment area will be billed directly to the participant’s insurance. In the rare instance that a participant might fail to obtain insurance, the study project will absorb some medical costs and a CPAP device will be dispensed as an in-kind contribution.

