### Phase V: debriefing and exit interviews

#### Exit interviews

At the end of the 12 month enrollment in the study, all participants will be debriefed by the project coordinator. Participants will complete the same baseline questionnaires and additional questionnaires designed to understand why participants adhered to the intervention and how the intervention might be refined to be more effective.

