### Limitations and challenges

Our study has several potential design and analytical limitations and challenges. A primary design challenge is to uphold blinding of participant assignment among key personnel. Only the project coordinator and data manager are aware of participant assignment to either the treatment or intervention group. To safeguard against unblinding, we have set up a very strict policy as to who can have access to data (blinded personnel do not have access to data), how project details are communicated in the team where all data are de-identified, and periodic checks to ensure integrity of data will be made by the data manager, who does not attend research project team meetings nor receives project-related email correspondence. A primary analytical challenge is our use of GEE, which is ideal to test our hypotheses and deal with unmeasured dependencies between outcomes. However, GEE requires a large sample size, which the study is powered for, but if we do not meet adequate sample size our power to make meaningful inferences using GEE will be compromised. As an alternative analytical plan, we would use analysis of covariance, which will improve our ability to detect significant effects on our primary and secondary outcomes using a smaller sample size.

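### Blind 6- and 12-month ascertainment is assigned to a staff member who knows the allocation, and close-out of OSA-negative participants conflicts with the follow-up promised to everyone

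*Protocol article*

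**What the plan says.** On blinding, Data collection and management has contact details passed to the data manager, "who will maintain a registry of enrolled participants (control group and intervention group"), and then says that "the data manager will perform blind outcome ascertainment at 6 and at 12 months". The section on allocation and blinding says: "All study staff except for the data manager and project coordinator will be blinded to participant assignment". It adds: "The data manager generates the randomization sequence for each eligible participant". Limitations and challenges repeats the position: "Only the project coordinator and data manager are aware of participant assignment to either the treatment or intervention group" (presumably meaning the two arms). Under Exit interviews, at the end of the 12 months, "all participants will be debriefed by the project coordinator", and participants repeat the baseline questionnaires.

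On completeness, Methods and design promises: "Regardless of group assignment, we will ascertain all outcomes at baseline and at 6- and 12-month follow-up assessments". The primary-aim analysis is by intention to treat. Yet the section on the sleep home study sends participants who do not meet OSA criteria to the project coordinator, "either for study close-out since they no longer need to continue their participation in the study", or for a later clinic-based assessment, or for treatment customization. It gives no rule for choosing among these three routes.

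**The concern.** The plan presents blind ascertainment as a safeguard but assigns it to one of the only two people who are declared unblinded. A reader of the trial report would credit a protection that the described arrangement does not give. The outcomes most open to this are those gathered by questionnaire: self-efficacy, apnea knowledge and functional outcomes.

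The close-out rule is a second and separate matter. A participant must have done the home study before it can be negative, and doing the home study is the primary outcome that the intervention is meant to increase. Departure by this route therefore depends on the outcome and, if the intervention works, on the arm. The 6- and 12-month questionnaires and the mediation analysis would then rest on groups from which adherent, OSA-negative members had been removed unequally.

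**Working it through.** **Blinding (no arithmetic).** Setting the statements side by side:

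- Person who ascertains outcomes at 6 and 12 months: the data manager (Data collection and management).
- Staff exempt from blinding: the data manager and the project coordinator (allocation and blinding; repeated under Limitations and challenges).
- Person who generates the sequence: the data manager.
- Person who debriefs at month 12: the project coordinator (Exit interviews). The text does not say who administers or scores the questionnaires.

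The first three cannot all stand together with the word blind.

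**Close-out: inputs.**

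- Arm size 199; planned rates 41% and 26%, given as 82 and 52 people (Sample size and power analysis).
- Reproduction: 0.41 × 199 = 81.6, rounded to 82; 0.26 × 199 = 51.7, rounded to 52. Both agree.
- OSA-negative share q among those who do the home study: not given at the trial's AHI cut-off of 10. There are two hints. The ARES section gives a positive predictive value of 0.91, so 1 − 0.91 = 9% negative, but for AHI > 5; a cut-off of 10 would give more negatives. The background cites a previous study in which 90% of those evaluated were diagnosed, so 10% negative. I use q = 10% to 30% as an assumed range.

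**Formula.** Close-outs per arm = number with a home study × q, taking q equal in both arms and every negative participant as closed out (an upper bound).

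| q (assumed) | Intervention: 82 × q | Control: 52 × q | % of 199 | Gap |
|---|---|---|---|---|
| 10% | 8.2 | 5.2 | 4.1 vs 2.6 | 1.5 points |
| 20% | 16.4 | 10.4 | 8.2 vs 5.2 | 3.0 points |
| 30% | 24.6 | 15.6 | 12.4 vs 7.8 | 4.5 points |

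The ratio is 82/52 = 1.58 whatever q is.

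**Effect on the primary outcome.** Home study received, yes or no, is known before close-out can occur. With 199 per arm kept in the denominator, the planned difference stays at 41 − 26 = 15 points. Only if closed-out people were dropped would it change. At q = 20%, the intervention rate becomes 0.41 × 0.8 / (1 − 0.41 × 0.2) = 0.328/0.918 = 35.7%, the control rate 0.26 × 0.8 / (1 − 0.26 × 0.2) = 0.208/0.948 = 21.9%, and the difference 13.8 points. Intention to treat, as stated, rules this out.

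**The case against.** The strongest reply on blinding is that the data manager, under Limitations and challenges, stays out of team meetings and project email, and that ascertainment may mean only tracking from computer-generated schedules. The first point protects other staff from learning the allocation; it does not make the data manager blind. The second may be what was intended, but then the text should say so and name the blinded assessor, which it does not.

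On close-out the reply has more force, and several stronger readings that a reader might infer are not supported.

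- *That the primary result is damaged.* It is not, for the reason shown in the working. CPAP adherence is measured by telemetry and does not concern participants without OSA.
- *That all OSA-negative participants leave.* Close-out is one of three routes, and Exit interviews speaks of all participants at month 12. The sentence could mean leaving the care pathway only. Its stated reason, however, is that participation need not continue, so the conflict with the follow-up promise stands.
- *That 82 and 52 are simply home-study counts.* The sample-size section first describes them as people who completed everything, follow-up included. It then uses the same 41% and 26% as evaluation rates for the primary outcome. Taking them as home-study rates is an assumption.
- *That the negative share is far higher.* One can back-calculate about 41% from 39% at risk, sensitivity 0.94 and specificity 0.79: prevalence = (0.39 − 0.21)/(0.94 − 0.21) = 0.247, and 1 − 0.94 × 0.247/0.39 = 0.41. This contradicts the predictive value of 0.91 in the same ARES section and refers to AHI > 5, so I do not rely on it.
- *That close-outs add to the 35% attrition.* The article does not say whether the 35% includes them.
- *That the coordinator collects the exit questionnaires, or that the questionnaire analysis drops incomplete cases.* Neither is stated. Data collection and management names Heckman and EM approaches and a comparison of withdrawals with completers. These address refusal and attrition; close-out directed by the protocol itself is not mentioned.

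**Conclusion.** Both points hold as contradictions within the article, and they differ in certainty. The blinding conflict is explicit and needs no assumption: as written, the 6- and 12-month ascertainment is not blind. The close-out conflict is also in the text, but its size is conditional. An excess of about 1.6 to 1 in the intervention arm requires that uptake follow the planned 41% vs 26% and that the negative share be equal in the arms; with no effect on uptake there would be no excess. The head counts, about 8 vs 5 at 10% negative and 25 vs 16 at 30%, are upper bounds on an assumed share. The consequence is confined to the 6- and 12-month questionnaire measures and the mediation analysis. This should be corrected, but it does not threaten the home-study comparison so long as all randomized participants stay in the denominator.

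**What to change.** 1. Name staff who are blinded under the allocation section, for example the research assistants, to collect the 6- and 12-month outcomes and the exit questionnaires, and limit the data manager to scheduling and tracking. If that is not feasible, withdraw the word blind from Data collection and management.
2. Reconcile the Phase III close-out sentence with Methods and design and with Exit interviews. State that close-out ends only the care pathway, and that these participants keep their 6- and 12-month assessments and stay in the intention-to-treat denominator.

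The cost is some reassignment of tasks among existing staff and a modest number of follow-up visits that might otherwise have been skipped. Those visits are already planned in Methods and design, and the Compensation section provides US$ 30 for each. Recruitment was still ongoing according to Trial status, so both changes could apply to later participants.

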#### Randomization to intervention or attention-control groups: allocation and blinding

Participants will be randomly assigned to either the intervention arm (partnered with a peer health educator who received the culturally and linguistically tailored sleep health education and was trained for 8 weeks) or the attention-control group (the comparative group where participants are partnered with a peer health educator who did not receive tailored sleep health education but only standard health training for a 1 hour session). The unit of randomization is the participant and thus the unit of analysis will be at the participant level. All study staff except for the data manager and project coordinator will be blinded to participant assignment. The data manager generates the randomization sequence for each eligible participant and the study coordinator randomly assigns peer health educators to participants assigned to treatment and attention-control groups. We will un-blind participant assignment only in cases where the participant’s health is at risk due to CPAP usage (Fig. 3).

##### Intervention group

Participants in the intervention arm of the study will receive counseling from peer health educators who received culturally and linguistically tailored sleep health education. The details and contents of peer health educator training are described in the Peer Health Educator Training section above. Participants will receive up to 10 sessions from their health educator with the hopes of motivating the participant along the OSA continuum of care, which entails screening, home-study assessment, sleep clinic assessment, diagnosis, treatment customization, and treatment adherence.

